### Outcomes

**Primary outcome **measures are:

1. Longitudinal change in the 17-item observer rated Hamilton Depression Rating Scale (HDRS) [23,28] from baseline to 6 and 12 months as well as follow up assessments at 18 and 24 months. The primary analysis will be change over the baseline to 6 and 12 months. The purpose of the analysis at 18 and 24 months is to determine if any change is maintained once the patient has been discharged from the specialist depression disorder team.

2. Change in global assessment of function [24] from baseline to 6 and 12 months as well as follow up assessments at 18 and 24 months.

**Secondary outcome **MEASURES ARE:

1. Change in self-rated depression: a) self-rated Beck Depression Inventory version 1 [29], a measure of cognitive symptoms of depression from baseline to 3, 6, 9, 12, 18 and 24 months; b) Personal Health Questionnaire [30] from baseline to 3, 6, 9, 12, 18 and 24 months, rating of depression severity according to DSM-IV criteria; c) Quick Inventory for Depressive Symptomatology self rated version [31] from 3, 6, 9, 12, 18 and 24 months, a 16-item screening/diagnostic questionnaire rating depression severity according to DSM-IV criteria. The last scale has the best established psychometric data for remission compared to the Hamilton Depression Rating Scale. The other two scales are widely used in clinical practice by general practitioners and psychotherapy services in England and Wales.

2. Euroqol 5 D [32] as a measure of quality of life and costs from health and social care and society perspectives measured at 6, 12, 18 and 24 months. Use of the EQ5 D will enable utility score sto be gained from the patients that may then be used in a cost utility analysis

3. Change in social adjustment [33], an assessment of social and occupational functioning from baseline to 6, 12, 18 and 24 months.

4. Patient satisfaction and relationship with the clinician(s) on a four part 9-item questionnaire based on two other questionnaires used frequently in depression studies: the Patient Satisfaction Questionnaire [34] and the Patient Doctor Relationship Questionnaire [35]. These will be measured at 6, 12, 18 and 24 months.

**Process measures**, which will not be utilised to determine the effectiveness of the interventions, but will be used to understand the processes that are taking place:

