### Sample size and justification

Sample size calculation was based on improvement in global assessment of severity in a study using a similar design, except that it employed a mixed diagnostic group rather than moderate to severe primary depressive disorder [14], 90% power, 2 tailed difference at 5% significance, 20% loss to follow up was 52 per treatment group (104 in total). However, this study did not employ an intention to treat analysis and there was a 30 percent loss to follow-up; therefore, the sample size has been inflated by a further 43 percent to 74 per group (148 in total). A further correction is to be made for the variability in the individual treatment from the SDDT and treatment as usual. A multiplicative correction factor to the sample size estimate of 1.18 calculated from [1 +rho*r/(1-rho)] [48] where rho is the intraclass correlation of 0.051[49] and r is the number of patients from each community mental health team (CMHT) per treatment arm (3-4). Therefore, the sample size is 87 per treatment group (174 in total). Sample size calculations were checked against a study of in-patient delivered combined psychotherapy and pharmacotherapy versus treatment as usual for patients with chronic depressive disorder [15]. The primary outcome variable was the 17-item Hamilton Depression Rating Scale (HDRS) and patients were followed up for 12 months. At baseline the combined treatment mean (sd) HDRS was 25.6 (4.4) and for clinical management it was 23.5 (4.8). At 12 months the HDRS score was 5.9 (5.1) in the combined treatment group and 11.3 (10.5) in the clinical management group (intention to treat analysis). Using a 2-tailed students t-test, 90% chance of detecting a difference at 0.05 level, and an effect size of 0.65, 51 patients per group are required (102 in total). If a 20 percent drop-out is assumed, then 122 patients (61 in each group) are required. Using the correction factor of 1.18 previously justified results in a sample size of 146 (73 in each group). In line with the more conservative estimate of the power of the study our aim is to recruit 87 patients per treatment group (174 in total).

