### Statistical analysis

Statistical analysis for quantitative measures will be on the 'intention-to-treat' basis and carried out by the research team in two stages. At the first stage, analysis will be focused on process measures. Differences at each time point and in changing patterns over time between the two treatment groups and amongst clinical sites will be examined. Results from such analysis will help us to identify possible covariates or confounders at the individual level or clinical level that may need to be adjusted for when comparing the primary of secondary measures between treatment groups. Mechanism of missing data on major outcomes will be examined by sensitivity analysis, to inform adequate imputation procedures. At the second stage, the HDRS of the primary measure as well as multiple secondary measures will be analysed separately and jointly. As all measures are taken longitudinally, multilevel models for repeated measures will be used [49]. Data of patients who dropped out or not completed follow-up measures will be analysed in the manor of last-observation-carried-forward in multilevel modelling. The core model for each measure will be two-level with individuals as level 2 units and time occasions as level 1 units. If random effects or large variation among clinical sites are detected in the first stage analysis, the core model will be extended to three-level with clinical sites at the top of the hierarchy as level 3 units to account for random effects among clinics. For analysing multiple measures (or multiple end points) simultaneously to investigate global change or multi-dimensional change of the intervention effects, the core model will also be extended to a three-level structure with measures at the bottom of the data hierarchy. All models will estimate the mean changes of measures from the baseline to the later time points for each treatment group, and differences in such changes between groups by interaction terms between time and treatment group in models, adjusting for possible confounders or covariates. For continuous measures with reasonably symmetric distribution, ordinary multilevel models will be used in the analysis. Otherwise, data transformation before model fitting will be considered. For count data with a long tail in the distribution, multilevel Poisson models will be considered [50]. For ordinal measures, multilevel multinomial models will be considered [51]. Descriptive and simple statistical analysis will be performed in SPSS and MLwiN [52] will be used for multilevel models analysis.

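### The treatment effect is defined as a group difference in change from baseline, with no stated adjustment for the baseline score

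*Protocol article*

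**What the plan says.** Under Outcomes, HDRS and GAF are both defined as change from baseline. For HDRS the article adds: "The primary analysis will be change over the baseline to 6 and 12 months".

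Under Statistical analysis, the model is given as follows: "The core model for each measure will be two-level with individuals as level 2 units and time occasions as level 1 units". On what is estimated, the section says: "All models will estimate the mean changes of measures from the baseline to the later time points for each treatment group". The effect is specified as "differences in such changes between groups by interaction terms between time and treatment group in models, adjusting for possible confounders or covariates".

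The covariates come from a first-stage analysis of the process measures: "Results from such analysis will help us to identify possible covariates or confounders at the individual level or clinical level". HDRS is a primary outcome and is not in the article's list of process measures, so baseline HDRS is not a named covariate. The article does not say whether each arm has its own baseline mean or whether one mean is shared.

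**The concern.** In a repeated-measures model with baseline as one of the occasions, the default fit includes a group term at baseline. The time-by-group interaction is then the difference in mean change. It subtracts the baseline difference between arms with a fixed coefficient of 1, however weakly baseline predicts the later score.

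Randomisation makes the true baseline means equal, so any observed gap is chance. Adjustment removes only the part of that gap which carries through to follow-up. Full subtraction overcorrects when the regression slope of follow-up on baseline is below 1 and undercorrects when it is above 1.

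At stake are some precision and the stability of the HDRS estimate in the one trial that is actually run. Randomisation is stratified by Trust only, so nothing in the design balances baseline HDRS directly. The Weaknesses section itself concedes that the study may be underpowered.

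**Working it through.** **The plan's own figure.** Sample size and justification cites a study with 12-month HDRS of 5.9 (SD 5.1) and 11.3 (SD 10.5).
- Average 12-month SD: s1 = √((5.1² + 10.5²)/2) = 8.25.
- Effect size: (11.3 − 5.9)/8.25 = 5.4/8.25 = 0.65, as stated.
- The article says: "90% chance of detecting a difference at 0.05 level, and an effect size of 0.65, 51 patients per group are required". A two-sample t-test calculation gives 50.7, so 51 is reproduced.

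This check therefore uses the 12-month score and its SD.

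**Other inputs.** Baseline SDs in the same study are 4.4 and 4.8, so s0 = √((4.4² + 4.8²)/2) = 4.60. The baseline-to-12-month correlation r is not given and is assumed over a range.

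**What the interaction estimates.** In 200 simulated trials with 87 per arm, baseline and two follow-ups, complete data and a free baseline mean per arm, the 12-month time-by-group term equalled the raw difference in mean change to within 7 × 10⁻¹³.

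**Variance comparison (per patient).**
- Change: s0² + s1² − 2·r·s0·s1 = 21.2 + 68.1 − 76.0·r.
- Baseline-adjusted: s1²(1 − r²) = 68.1(1 − r²).
- The difference is (s0 − r·s1)², which is never negative.

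| r | Change | Adjusted | Variance cut |
|---|---|---|---|
| 0 | 89.3 | 68.1 | 24% |
| 0.2 | 74.1 | 65.4 | 12% |
| 0.3 | 66.5 | 62.0 | 7% |
| 0.5 | 51.3 | 51.1 | 0.4% |

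The loss vanishes at r = s0/s1 = 0.56 and is about 4% at r = 0.7.

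**Power.** Take an effective size of 87 × 0.8/1.18 = 59 per arm (the plan's 20% dropout and 1.18 correction) and a 5.4-point difference. Power for change versus adjusted is 87% versus 94% at r = 0, 93% versus 95% at r = 0.2, 95% versus 96% at r = 0.3, and 98% for both at r = 0.5.

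**Chance imbalance.** The SE of the baseline difference at 87 per arm is 4.60 × √(2/87) = 0.70, giving a 95% range of about ±1.4 points. Each point of gap moves the change estimate relative to the adjusted one by 1 − r·s1/s0, where s1/s0 = 1.79:
- r = 0.2: 0.64
- r = 0.3: 0.46
- r = 0.5: 0.10

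A gap at the 95% limit therefore moves the estimate by about 0.9, 0.6 and 0.14 points respectively.

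**Simulation check at r = 0.4 with the cited SDs.** The empirical SE of the 12-month effect was 1.18 for change, 1.16 for the same model with a common baseline mean, and 1.15 for analysis of covariance. The correlation of the estimate with the chance baseline gap was −0.22 for change and −0.05 for analysis of covariance.

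**The case against.** The strongest reply is that the article never says the arms have separate baseline means. A model with one shared baseline mean also yields differences in change through time-by-group terms, fits the quoted sentences, and performs close to analysis of covariance. The article is condensed, and the full plan may settle this. That stands: it cannot be said that the authors rejected baseline adjustment. What remains is that the article fixes the contrast and the source of the covariates, and on the default fit the result is unadjusted.

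The second reply is that the loss is small on the plan's own figures. This also largely stands. With 59 per arm effectively, power stays above 90% at r = 0.2 and higher, and only r near 0 falls below.

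Several stronger readings are tempting, and the documents do not support them.
- A reader might infer that the analysis is biased or invalid. Randomisation keeps the change estimate unbiased on average.
- A reader might set the cited study's 7.5-point difference in change against its 5.4-point endpoint difference and take the gap as the size of the problem. The proper comparator is the adjusted estimate, 5.4 + 2.1 × slope, where the slope is r·s1/s0. That is 6.53 at r = 0.3 and 7.28 at r = 0.5. A 2.1-point baseline gap would also be a 3-SE event in this trial.
- Equal SDs at baseline and follow-up would imply larger losses, but the cited SDs are not equal, and the HDRS entry threshold of 16 tends to narrow the baseline SD.
- A reader might infer that the two-level model assumes equal variances and so gives wrong standard errors. The article does not state the covariance structure, the 6-month SD or the correlations, so neither the sign nor the size of any error can be determined.
- A reader might infer that sizing on the 12-month score undermines the sample size. Change has the smaller variance once r exceeds s0/(2·s1) = 0.28, and the target of 87 per arm came from the other calculation, on global severity.

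**Conclusion.** The point holds as an efficiency and conditional-imbalance weakness with an easy remedy. It is not an error that invalidates the analysis. As written, the effect is a difference in change with no stated baseline adjustment. With free baseline means this gives up about 24% of the variance at r = 0, 7% at r = 0.3 and almost nothing at r = 0.5, and leaves the estimate exposed to a chance baseline gap with an SE of 0.70 points.

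These sizes rest on the SDs of one cited in-patient study averaged over its arms, on assumed correlations common to both arms, on complete data, and on baseline means that are not constrained. If the full plan already uses a common baseline mean or a baseline covariate, only the article's wording needs clarifying.

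**What to change.** State in the Statistical analysis section that the 6- and 12-month HDRS contrasts will be obtained in one of two ways:
- follow-up scores as outcomes, with the baseline score as a covariate; or
- baseline kept as an occasion, with its mean constrained equal across arms.

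Name the one chosen, and report the adjusted group difference at each time point. Apply the same rule to GAF and to the secondary scales that have a baseline measurement.

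The cost is a sentence or two of analysis wording, settled before unblinded data are seen. Baseline scores are already collected, so no visits, measures or patients are added. On the formulas above, large-sample precision is not reduced at any correlation.

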
### Health economics

We will ascertain health, social and personal costs and examine cost utility and cost effectiveness from health and social care, and societal perspectives. The aim is estimation in relation to NICE thresholds for cost effectiveness rather than significance testing [8]. At baseline, 6 and 12 months the research associate will interview patients using a modified version of the Client Service Receipt Inventory [53]. At 3 and 9 months a modified self-report version of the Client Service Receipt Inventory will be mailed out to patients. At baseline and 12 months the research associate will interview patients using a modified version of the Client Service Receipt Inventory [53]. This inventory records inputs given by family members as a result of the patient's depression, as well as the amount of time off work by the patient and any carer due to depression including the costs of such. Data on social security payments will also be collected by qualitative interview. Nationally applicable unit costs [54] will then be combined with the service user data to generate service costs. Medication costs will be obtained from the British National Formulary and hospital based costs will be obtained from NHS reference costs. The cost of the specialist intervention can be calculated with the help of diaries showing time spent by the different members of the team in delivering the work of the specialist mood disorders team together with these unit health costs. Interviews with treatment as usual teams will generate estimates of all hidden costs for team discussion and supervision that the patient will not be aware of. Costs of time off work will be calculated from the patient's own account of their salary and normal expectations of overtime and informal care to the depressed patient will be calculated at the commercial rate that a carer would have to be paid through an agency. Personal information that may identify the participant will not be collected during these questionnaires and qualitative interviews; therefore, confidentiality will be maintained.

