8. At baseline, 6, 12, 18 and 24 months, participants' overall tendencies to avoid thinking about painful emotional issues will be measured using The Acceptance and Action Questionnaire-1 [46]. Patients who score highly on this measure are likely to need more preparation before they can undertake psychological treatment.

All measures will be assessed at baseline, 6, 12, 18 and 24 months face-to-face by the research associate (unless otherwise stated). At 3 and 9 months the Beck Depression Inventory, the PHQ-9, the QIDS-SR and a questionnaire version of the health economics interview will be mailed to all participants.

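### Costs are a secondary outcome at 6, 12, 18 and 24 months, but the service-use inventory that supplies them is scheduled at no time after month 12

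*Protocol article*

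**What the plan says.** Under secondary outcomes, the Outcomes section of the protocol article pairs the EQ-5D with "costs from health and social care and society perspectives measured at 6, 12, 18 and 24 months".

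The Health economics section describes how the cost data are obtained. The instrument is a modified Client Service Receipt Inventory, and three sentences give its times:

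- The first sets the interview times: "At baseline, 6 and 12 months the research associate will interview patients using a modified version of the Client Service Receipt Inventory".
- The next adds a self-completed form of the same instrument, sent by post at months 3 and 9.
- The last sets interview times again, this time without month 6: "At baseline and 12 months the research associate will interview patients using a modified version of the Client Service Receipt Inventory".

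The third sentence leads directly into the items on family input and on "the amount of time off work by the patient and any carer due to depression". Unit costs "will then be combined with the service user data to generate service costs".

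The Outcomes section closes with a general rule: "All measures will be assessed at baseline, 6, 12, 18 and 24 months face-to-face by the research associate (unless otherwise stated").

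**The concern.** The two sections give different times for the same outcome. One promises costs at four follow-up points out to month 24; the other lists the collection of the underlying data and stops at month 12. This is not detail that the article leaves to a fuller document, because the article states a schedule in both places and the two disagree.

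Cost effectiveness is half of the first objective, and the Design section asks whether any difference lasts to month 24, a year after discharge from the specialist team. If site staff follow the Health economics section, informal care and lost work in months 12 to 24 will not be asked about at the time and cannot be reliably recovered afterwards. The EQ-5D would exist at 18 and 24 months with no matching costs, so a cost-utility estimate to month 24 could not be made.

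A lesser mismatch of the same kind concerns the audit against NICE guidelines. The process measures in Outcomes confine it to the 12-month follow-up, whereas the Strengths part of the Discussion relies on it for two years.

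**Working it through.** The plan gives no figure to reproduce here. The check compares the stated schedules as sets of months.

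**Inputs**

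- Cost outcome times (Outcomes, secondary outcome 2): {6, 12, 18, 24}
- Inventory interview, first statement (Health economics): {0, 6, 12}
- Inventory by post (Health economics, and consistent with the end of Outcomes): {3, 9}
- Inventory interview, second statement (Health economics): {0, 12}
- Length of follow-up (Design): 24 months

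**Coverage, taking all inventory statements together**

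- Inventory times: {0, 6, 12} ∪ {3, 9} ∪ {0, 12} = {0, 3, 6, 9, 12}, five points, none after month 12.
- Cost times without an inventory: {6, 12, 18, 24} minus {0, 3, 6, 9, 12} = {18, 24}, which is 2 of 4 (50%).
- Follow-up without patient-reported service use: 24 − 12 = 12 of 24 months.

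**Coverage if the second interview sentence governs**

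- Inventory times: {0, 12} ∪ {3, 9} = {0, 3, 9, 12}.
- Cost times without an inventory at that visit: {6, 18, 24}, which is 3 of 4. This is conditional; nothing in the text says the second sentence overrides the first.

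**Does the general visit rule fill the gap?** It gives way wherever other times are stated, and the Health economics section states other times. If the rule were nevertheless meant to prevail, the list in Health economics would be wrong and would still need correcting.

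**Do the other cost sources fill the gap?**

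| Source | What it supplies | Months 12 to 24? |
|---|---|---|
| Unit costs | Prices, to be applied to service-use data | Unusable without the inventory |
| Specialist team diaries | Cost of the team's own work | Patients are discharged from the team at month 12 |
| Interviews with usual-care teams | "estimates of all hidden costs for team discussion and supervision that the patient will not be aware of" | No times given; not patient service use |
| Interviews on social security payments | Benefits received | No times given |
| Case-note audit | Some mental health contacts | Possibly, but not informal care or time off work |

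**Recall period needed to close the gap.** The article gives none, so this is an assumption. With six-month recall, inventories at months 18 and 24 cover 6 + 6 = 12 of the 12 missing months. With three-month recall they cover 3 + 3 = 6 of 12.

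**The case against.** The strongest reply is that the Health economics section never says that collection ends at month 12. The Outcomes section twice points the other way, once for costs and once in its general visit rule. Two nearly identical sentences with different times look like an editing slip rather than a decision, and the full protocol may hold a correct visit table. All of that is plausible. It explains how the conflict arose and suggests which version was intended, but the published text still gives an explicit list that stops at month 12, and one of the two sections has to change.

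Three narrower points have some force:

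- No 24-month horizon is fixed for the economic evaluation, and the Outcomes section presents cost-utility analysis only as a possible use of the EQ-5D. The first objective could therefore be answered at 12 months, when specialist treatment ends. What is at risk is the later half of one secondary outcome.
- The count of 3 of 4 depends on the second sentence governing. Even then, postal inventories at 3 and 9 months plus the 12-month interview might span the first year, depending on recall. The firm count is 2 of 4.
- Case notes, which the Treatment as usual section says will be audited, could recover some mental health contacts. This narrows the gap for service costs but leaves informal care and lost work untouched.

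The audit mismatch concerns a process measure that is not used to judge effectiveness. It is real but minor.

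**Conclusion.** The concern holds. As written, 2 of the 4 cost time points have no data collection behind them, and 12 of 24 months of follow-up carry no patient-reported service use, informal care or time off work. The Health economics section also contradicts itself on whether the inventory interview takes place at month 6.

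This rests on two readings: that the four times in secondary outcome 2 apply to costs as well as to the EQ-5D, which is the natural sense of the sentence, and that a specific schedule overrides a general rule that yields to one.

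The sponsor should correct it before patients reach month 18, but it does not threaten the trial's main conclusion. The primary analysis over 12 months, the sample size, the HDRS and GAF comparisons at 18 and 24 months, and costs to month 12 do not depend on later inventories.

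**What to change.** In Health economics, give one interview schedule for the inventory: baseline, 6, 12, 18 and 24 months, with the postal version at 3 and 9 months. Delete the second interview sentence, so that the informal-care and time-off-work items follow the same schedule. State a six-month recall period at months 18 and 24, so that together the two visits cover months 12 to 24. If the sponsor in fact means costs to stop at month 12, the text can be made consistent by shortening the cost times in Outcomes instead, but the 18- and 24-month cost outcome is then given up.

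Separately, state in the process measures the two-year audit window that the Discussion relies on. Whether the three-month blocks continue after month 12 can be left to the sponsor.

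**Cost.** No new visits are needed, since face-to-face assessments at 18 and 24 months are already planned. The burden is a longer interview at each: at most 2 × 174 = 348 inventories beyond those listed in Health economics. Applying the losses of 20% and 30% mentioned in Sample size and justification gives 348 × 0.8 = 278.4 and 348 × 0.7 = 243.6, or about 278 and 244. The audit change means case-note review of months 12 to 24, which the Discussion already promises.
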